#### 10.4 Handling of Serious Adverse Events

All adverse drug events encountered during the clinical study will be reported on the CRF. Serious adverse events (SAEs), whether or not associated with study medication administration, will be recorded both on the Adverse Event form of the CRF as for non-serious AE and the SAE form.

ALL SAEs occurring during this study and up to 30 days after a subject discontinued or completed the study, whether or not related to the administration of study medication, must be reported by faxing the completed SAE form, after reviewing the report for consistency and accuracy within 24 hours of awareness by the investigator, to KAIMRC / IRB.

As far as possible, investigators should follow-up participants with AEs until the event is resolved or until, in the opinion of the investigator, the event is stabilized or determined to be chronic. Details of AE resolution must be documented in the CRF. Participants should be followed-up for 30 days after receiving the last dose of study medication and any AEs, which occur during this time, should be reported according to the procedures outlined above. Any significant changes in AEs should be reported even though the subject has completed the study, including the protocol-required post-treatment follow-up.

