| Number of subjects         | 520 (260 per group).                                                                                                                                                                                                                                                                                                                                                                                                                                                                                                                                                                                                                                                                                                                        |
| Study product              | 
Route of Administration: Oral (or through Nasogastric tube)
 
Dose:
 
Favipiravir: Administer 1800 mg (9 tablets) by mouth twice daily for one day, followed by 800mg (4 tablets) twice daily (total days of therapy is 10 days or till hospital discharge)
 
Hydroxychloroquine (400mg) twice daily on day 1; for days 2-5 (200mg) twice daily.
                                                                                                                                                                                                                                                                                                                                                                      |
| Duration of administration | 
Favipiravir: 10 days
 
Hydroxychloroquine: 5 days
                                                                                                                                                                                                                                                                                                                                                                                                                                                                                                                                                                                                                                                                               |

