| Safety End Points   | This study will be able to determine the safety of investigational therapeutics to determine if the rate of AEs is higher, lower, or no different than control arm.                                                                                                                                                                                                                                                                                                                                                                                                                                                                                                                                                                                                                                                                                                                                                                                                                                                                                                                                                                                                                                                                                                                             |

|                               |                                                                                                                                                                                                                                                                                                                                                                                                                                                                                                                                                                                                                                                                                                                                                      |

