#### Reference Therapy:

Standard of care is defined as: Treatment that is accepted by medical experts as a proper treatment for Covid-19 disease. Standard care comprised, as necessary, supplemental oxygen,

noninvasive and invasive ventilation, antibiotic agents, vasopressor support, renal-replacement therapy, extracorporeal membrane oxygenation (ECMO), and antiviral therapy except Favipiravir. Also, it may include intravenous fluids and medications for symptoms relieve.

Although it would not be preferred to use medication that has antiviral activity, the treating physician would have the authority/ autonomy to start the patient on antiviral but not Favipiravir, i.e., Lopinavir–Ritonavir, interferon, ribavirin, Hydroxychloroquine or Remdesivir). Anyone of those medications with possible antiviral activity against SARS-CoV-2 would be accepted to be used in the case that treating physicians thought it would be the best of interest for the patient.

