### 7.2 Treatment Period

The treatment intervention would be for a maximum of 10 days from randomization and it would be as follow:

Favipiravir for 10 days as follow:

Administer 1800 mg (9 tablets) by mouth twice daily for one day, followed by 800mg (4 tablets) twice daily (total days of therapy is 10 days)

Hydroxychloroquine for 5 days:

(400mg) twice daily on day 1; for days 2-5 (200mg) twice daily.

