### 7.3 Safety monitoring

Site PI should follow on a daily basis all the possible AEs while using the investigational medications and up to day-14. This includes regular monitoring of hematology and blood chemistry. Daily ECG and QT interval monitoring. And LFT every other day. In case of any concerns that might require holding/stopping medication, causality assessment should be done by PI and with a consultation to an independent clinician.

Details of cardiac toxicity monitoring as follow:

1. A baseline ECG before starting then daily ECG after.
2. Daily ECG to be done through day 1-10 or twice daily if the corrected QT interval more than 480ms.
2. Maintain serum level of Mg>1.0 meq, and K>4.5 meq throughout the 10 days of therapy.
3. If the QTc prolonged more than 500ms after starting, stop the medication.
4. Avoid any other QT prolong medication during the regimen.
5. If the patient develops torsades de-pointes, stop the medication immediately, follow ACLS protocol and call the cardiologist on-call.

If you have any query or help, please call for cardiology team in you center.

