## 8. FLOW CHART

Table 4: Flow Chart

|                                                 | Study period |                 |    |     |    |     |    |     |     |     |     |          |
|-------------------------------------------------|--------------|-----------------|----|-----|----|-----|----|-----|-----|-----|-----|----------|
|                                                 | Baseline     | Post allocation |    |     |    |     |    |     |     |     |     | Closeout |
| Timepoint study days                            | D0           | D1              | D2 | D'' | D5 | D'' | D9 | D10 | D'' | D14 | D21 | D28      |
| Enrolment and assignment                 |              |                 |    |     |    |     |    |     |     |     |     |          |
| Eligibility assessment                          | X            | X               |    |     |    |     |    |     |     |     |     |          |
| Informed consent                                | X            | X               |    |     |    |     |    |     |     |     |     |          |
| Randomization                                   | X            | X               |    |     |    |     |    |     |     |     |     |          |
| Baseline data                                   | X            | X               |    |     |    |     |    |     |     |     |     |          |
| Study drug administration                |              |                 |    |     |    |     |    |     |     |     |     |          |
| Favipiravir                                     |              | X               | X  | X   | X  | X   | X  | X   |     |     |     |          |
| Hydroxychloroquine                              |              | X               | X  | X   | X  |     |    |     |     |     |     |          |
| Adverse effect reaction                         |              | X               | X  | X   | X  | X   | X  | X   | X   | X   |     |          |
| Serious adverse event assessment                |              | X               | X  | X   | X  | X   | X  | X   | X   | X   | X   | X        |
| Clinical data collection                 |              |                 |    |     |    |     |    |     |     |     |     |          |
| Seven-category ordinal scale and CRF            | X            | X               | X  | X   | X  | X   | X  | X   | X   | X   | X   | X        |

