### For secondary endpoints:

- Quantitative variables such as duration of ICU stay and change from baseline in clinical scores, etc., are expected to have reasonably skewed distributions and may be subject to censoring (e.g., for subjects in hospital on Day 28; these will be compared between randomized arms using non-parametric tests (e.g., Wilcoxon's Test adapted, if necessary, to handle censoring).
- Analysis of the ordinal scale endpoints will use a proportional odds model with an indicator variable for randomized treatment. The Wald test will be used to generate a p-value comparing treatments, as well as the estimated proportional odds ratio comparing treatments with associated 95% CI.

- Analysis of AE data will primarily be descriptive based on MedDRA coding of events. The proportion of subjects experiencing an SAE and the proportion experiencing a Grade 3 or higher AE will be compared between randomized arms using Fisher's Exact Test.

For enrolled subjects who were not randomized (i.e. screen failures) or who were randomized but did not receive the treatment, the final analysis will detail safety (deaths and SAEs), and reasons they were not randomized or did not received treatment respectively.

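### The Protocol gives conflicting AE collection windows, and the longest is counted from a last dose that controls do not have, so Grade 3 or higher AEs may be compared over unequal periods

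*Protocol*

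**What the plan says.** The Protocol describes AE collection in four places, and they do not agree.

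- **Section 7.3, Safety monitoring:** "Site PI should follow on a daily basis all the possible AEs while using the investigational medications and up to day-14".
- **Section 8, Table 4:** the row "Adverse effect reaction" is marked from D1 to D14 and is blank at D21 and D28. The SAE row continues to D28. The AE row is not split by arm, although the laboratory and ECG rows are.
- **Section 10.3:** every AE met during the study goes on the CRF, whether or not linked to study medication, with no day limit. Section 7.4 ends follow-up at discharge or day 28.
- **Section 10.4:** "Participants should be followed-up for 30 days after receiving the last dose of study medication and any AEs" arising in that time are to be reported.

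Section 10.4 also has a separate SAE rule, which runs to 30 days after a subject completes or discontinues the study.

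On dosing, Section 7.2 says "The treatment intervention would be for a maximum of 10 days from randomization", and the Protocol Summary says of favipiravir "total days of therapy is 10 days or till hospital discharge". For controls, the reference therapy text reads "Standard of care is defined as: Treatment that is accepted by medical experts as a proper treatment for Covid-19 disease". It defines no course and no last dose.

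On analysis, the safety endpoint in the Protocol Summary is "to determine if the rate of AEs is higher, lower, or no different than control arm". Section 9.4 states that "the proportion experiencing a Grade 3 or higher AE will be compared between randomized arms using Fisher's Exact Test", tests the SAE proportion in the same way, and treats other AE data mainly descriptively. It names no observation window.

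**The concern.** A crude proportion with at least one event rises with the time observed. Comparing two such proportions informs about the treatments only if both arms are observed for the same length of time.

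The Section 10.4 rule starts its 30 days at the last dose of study medication. That date exists for a patient on the combination and is not defined for a patient on standard of care. A site that follows the text could collect non-serious AEs to about day 40 in one arm and stop at day 14 or day 28 in the other. The trial is open label, so blinding does nothing to keep collection equal. Extra events would then appear on the combination through longer observation alone, and they would enter the Grade 3 or higher Fisher test and the descriptive AE tables.

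**Working it through.** The Protocol states no figure to reproduce here. The check has two steps: the length of the windows, and what unequal windows could do to the planned test.

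**Step 1: windows**

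Inputs: last dose no later than day 10 (Section 7.2); 30 days after the last dose (Section 10.4); day 14 (Section 7.3 and Table 4); day 28 (Section 7.4, read with Section 10.3).

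End of window on the combination = day of last dose + 30.

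| Last dose | Window ends | Ratio to day 14 | Ratio to day 28 |
|---|---|---|---|
| Day 1 | Day 31 | 31/14 = 2.21 | 31/28 = 1.11 |
| Day 5 | Day 35 | 35/14 = 2.50 | 35/28 = 1.25 |
| Day 10 | Day 40 | 40/14 = 2.86 | 40/28 = 1.43 |

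The window also varies within the experimental arm, because dosing may end at discharge.

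**Step 2: effect on the Fisher test (illustration)**

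The Protocol gives no AE rates, so the following are assumptions:
- 260 per arm (Section 9.2.2) and the same AE hazard in both arms, so no true difference.
- A 14-day risk p of a Grade 3 or higher AE of 5, 10 or 20%.
- A hazard after day 14 equal to f times the earlier hazard, with f = 1, 0.25 or 0.1.
- All combination patients followed to day 40, the longest case.

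For follow-up to day T:
- Effective exposure: E = 14 + f × (T − 14)
- Risk by day T: 1 − (1 − p)^(E/14)

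Example with p = 5%, T = 40:
- f = 1: E = 40, risk = 1 − 0.95^(40/14) = 13.6%
- f = 0.25: E = 14 + 0.25 × 26 = 20.5, risk = 7.2%
- f = 0.1: E = 14 + 0.1 × 26 = 16.6, risk = 5.9%

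The exact probability that a two-sided Fisher test at 0.05 declares an excess on the combination was obtained by summing over the two binomial distributions. Each cell gives control risk v combination risk, then that probability.

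| Windows (days) | Hazard after day 14 | p = 5% | p = 10% | p = 20% |
|---|---|---|---|---|
| 14 v 40 | constant | 5.0 v 13.6%: 92% | 10.0 v 26.0%: 99.7% | 20.0 v 47.1%: 100% |
| 14 v 40 | one quarter | 5.0 v 7.2%: 14% | 10.0 v 14.3%: 28% | 20.0 v 27.9%: 52% |
| 14 v 40 | one tenth | 5.0 v 5.9%: 5% | 10.0 v 11.7%: 7% | 20.0 v 23.2%: 12% |
| 28 v 40 | constant | 9.8 v 13.6%: 24% | 19.0 v 26.0%: 44% | 36.0 v 47.1%: 70% |
| 28 v 40 | one quarter | 6.2 v 7.2%: 5% | 12.3 v 14.3%: 8% | 24.3 v 27.9%: 13% |
| 28 v 40 | one tenth | 5.5 v 5.9%: 3% | 10.9 v 11.7%: 4% | 21.8 v 23.2%: 5% |

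For reference, with equal 14-day windows the two-sided false-positive rate is 3.2 to 3.8% over the same risks. By symmetry, half of that (1.6 to 1.9%) falls on the side of an excess on the combination.

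**The case against.** The other side has several good points.

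- **Onset dates are recorded.** Section 10.3 requires AE onset time and start and stop dates, so a SAP could cut both arms at a common day. The AE row of Table 4 applies to both arms, so day 14 is available for that purpose. A reader might infer that the safety objective cannot be answered at all; the Protocol does not support that. It remains true that an analysis rule cannot recover non-serious events that were never collected from controls after day 14. It also remains true that Section 9.4 fixes the test without a window.
- **SAEs are not exposed.** A reader might infer that both Fisher tests are distorted. They are not: the SAE window in Section 10.4 is tied to study completion or discontinuation in both arms, and the SAE row of Table 4 is common to both. What is exposed is mainly non-serious Grade 3 events after day 14.
- **40 v 14 is an extreme pairing.** It gives one arm the longest reading and the other the shortest. Section 10.3 covers both arms and supports day 28 for controls. No visit is scheduled after D28, so collection to day 40 has no planned contact behind it. A general threefold difference in follow-up therefore cannot be inferred; 2.86 is the maximum.
- **Section 9.1 counts standard of care as a study drug.** It does, but only to define that treatment was started. It gives controls no last dose.
- **The sentence stands in the SAE section** and may have been meant as a reporting rule for SAEs. It nevertheless says AEs of any kind, and SAEs already have their own 30-day rule in the same section with a different starting point.
- **A false harm signal is not certain.** The 92 to 100% figures need a constant hazard to day 40, which is doubtful in an acute illness. With a quarter hazard and a 5% risk, about 86% of trials would show no significant excess.

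**Conclusion.** The contradiction is in the text, and it can act differently in the two arms. The Protocol allows AE collection to day 40 on the combination against day 14 (2.86 times) or day 28 (1.43 times) on control. The direction of any bias is against the combination. It reaches the Grade 3 or higher Fisher comparison and the descriptive AE tables; the SAE comparison and the primary endpoint are untouched.

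The size cannot be fixed from the Protocol. Under the assumptions above it runs from near the nominal error rate (28 v 40 days, hazard reduced to a tenth) to near certainty (14 v 40 days, constant hazard). The calculation also assumes that later events enter the test without truncation, which the Protocol neither states nor rules out. This should be fixed, but it does not threaten the trial's main conclusion.

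**What to change.** Reconcile Section 7.3, Table 4, Section 10.3 and Section 10.4 to one AE window that is counted from randomisation and identical in both arms. State in Section 9.4 that the between-arm AE comparison uses only events with onset in that window.

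Either of two windows would serve:
- **Day 14:** already scheduled for both arms, so it adds no collection. Later non-serious AEs are left out of the comparison.
- **Day 28:** the existing close-out. It adds AE entries at D21 and D28, where SAEs and the ordinal scale are already recorded.

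The 30-day post-dose rule can remain for safety reporting, with a statement that events after the common window are listed but not compared. The cost is a wording amendment in these sections and, if day 28 is chosen, the additional AE entries in both arms.

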#### 10.5 Regulatory Responsibility

The sponsor has a responsibility to report to the regulatory authorities and Ethics Committee safety information according to the local regulations. Therefore, prompt notification of serious adverse events by the investigator is required so that reporting timelines can be met and also to ensure ethical responsibilities towards the safety of other subjects are met.

The sponsor will also inform all participating investigators and Ethics Committee according to the local regulations.

### 11. ETHICAL AND REGULATORY STANDARDS

#### 11.1 Ethics and Good Clinical Practices

This study must be carried out in compliance with the protocol and in accordance with the laws and regulations of Saudi Arabia, and the sponsor or their representative's standard operating procedures. These are designed to ensure adherence to Good Clinical Practice, as described in the following documents:

ICH Harmonized Tripartite Guidelines for Good Clinical Practice 1996.

- Declaration of Helsinki, concerning medical research in humans (Recommendations Guiding Physicians in Biomedical Research Involving Human Subjects, Helsinki 1964, amended Tokyo 1975, Venice 1983, Hong Kong 1989, Somerset West 1996, Edinburgh, Scotland, October 2000, Washington 2002, Tokyo 2004, Seoul, October 2008) Brazil, October 2013.

The Investigator agrees, when signing the protocol, to adhere to the instructions and procedures described in it and thereby to adhere to the principles of Good Clinical Practice that it conforms to. A copy of the Declaration of Helsinki is provided in the Investigator study file at each site.

### 11.2 Ethics Committee

Before implementing this study, the protocol, the proposed informed consent form and other information to subjects must be reviewed by an appropriate Institutional Review Board/Independent Ethics Committee (IRB/IEC). A signed and dated statement that the protocol and informed consent have been approved by the IRB/IEC must be given to the Sponsor before study commencement. The name and occupation of the chairman and the members of the IRB/IEC must be supplied to the Sponsor. Any amendments to the protocol, which need formal approval as required by local law, must be approved by this committee. The IRB may be notified of all other amendments (i.e. administrative changes).

The study may not start before written approval has been obtained for the protocol and the informed consent form.

### 11.3 Informed consent

In obtaining and documenting informed consent, the investigator should comply with the applicable regulatory requirement(s), and should adhere to GCP and to the ethical principles. Prior to the beginning of the trial, the investigator should have the IRB written approval of the written informed consent form and consenting process.

The investigator, or a person designated by the investigator, should fully inform the subject, subjects family or the subject's Legally Acceptable Representative (LAR), of all pertinent aspects of the trial including the nature of the study, its purpose, the procedures involved, the expected duration, the potential risks and benefits involved and any discomfort it may entail. All questions about the trial should be answered to the satisfaction of the subject or the subject's family member or subject's LAR.

Due to the nature of the study and the risk of spreading the virus to the study team, and after waiver is granted by the IRB, special measures related to the consenting and the documentation process will be implemented. These measures are:

- Prior to a subject's participation in the trial, the written informed consent form should be signed and personally dated by the subject and the PI and/or the delegated person who explained the trial to the patient, using two original copies, one to be given to the patient and one with the study team. . To reduce the risk of spreading the virus, the original consent forms will be kept in the secure place with minimal access in the hospital before filing.
- If the subject is unable to give the consent, a subject's family member or subject's LAR will give the consent. In some situations where the family or subject's LAR are not able to be present, an oral consent over the phone will be obtained in a timely manner followed by sending the consent form to be signed and collected via the email communication or mobile phone if possible at the earliest opportunity valuable or to be signed at a later time at the site when allowed.
- If a subject is unable to read or if a family member or subject's LAR is unable to read, then an impartial witness should present during the entire informed consent discussion, and signs the consent form in addition to the subject or the subject's family member or subject's LAR.
- Subjects who are unable to read and who do not speak Arabic nor English as their first language have the consent form read to them by a qualified interpreter and that the interpreter signs the consent form as well as the subject, subject's family member, subject's LAR and the PI.
- If the subject is unable to give a consent and has no family member or subject's LAR or in case the PI or the study team could not reach to a family member or subject's LAR after doing all possible efforts, the PI has to seek the consent from the subject's attending physician (most responsible physician) for the enrollment in the trial.
- Procedures to inform, at the earliest feasible opportunity, the subject (i.e., if his/her condition improves), a family member, a subject's LAR of the subject's inclusion in the trial, the details of the research, and the right to discontinue the subject's participation at any time without penalty or a loss of entitled benefits.

Any changes to the proposed consent form suggested by the investigator must be agreed to by the Sponsor before submission to the IRB/IEC and a copy of the approved version must be provided to the Sponsor after IRB/IEC approval.

